### Participant follow-up

Patients will also be followed up via the NHS Information Centre Medical Research Information Service for a minimum of 20 years after the end of study follow-up.

### Pregnancy

Women of childbearing potential (able to have children) are required to use reliable forms of contraception if taking part in the study (including barrier and/or oral methods). Women of childbearing potential will be excluded if planning pregnancy during the trial period or sexually active and not using a reliable form of contraception.

### Patient withdrawal

#### Temporary discontinuation of investigational medicinal product (IMP)

There should be no reason to discontinue the study drug unless in exceptional circumstances such as side effects, for example renal impairment or significant hypotension. In such cases, the investigator should downtitrate or discontinue the study medication as required. Reintroduction of the study medication should be monitored and uptitration undertaken as required.

#### Permanent discontinuation of IMP

Patients may permanently withdraw from treatment with the investigational medicinal product (IMP) if they decide to do so, at any time and for any reason, or this may be the investigator’s decision. If there is considered to be a concern about the batch of IMP, recall procedures will be in place and measures will be taken to ensure the safety of all trial participants.

### Withdrawal from trial procedures and incomplete follow-up

Patients are free to withdraw consent from trial procedures at any time. Investigators must ascertain the reasons for the withdrawal including discontinuation of study drug, withdrawal from study investigations and/or follow-up, withdrawal due to adverse events, failure to attend, non-compliance, withdrawal of consent, or other reasons. The withdrawal form must be faxed to the CTEU within 5 working days, unless withdrawal is due to a SAE, in which case the investigator will follow SAE reporting procedures.

Withdrawal from trial procedures may result in incomplete patient follow-up and failure to capture outcome data. In these cases as much data as possible will be collected, up until the point of withdrawal. Patients may choose to withdraw from trial procedures and request that further data are not collected.

### Enrolment and participating centers

Based on 26 centers recruiting, we expect an approximate recruitment rate of one patient/month/center, which will enable 490 patients to be recruited over a 2-year enrolment window. The study will run for 66 months (5.5 years) split into four periods as follows:

1. Start-up: 6 months

2. Enrolment: 24 months (with potential to extend into the third year if necessary)

3. Follow-up: 36 months minimum (patients enrolled at the start of the study will be followed up for a maximum of 60 months, thus the mean follow-up period is 48 months)

4. Closeout: 6 months.

### Outcome measures

#### Primary outcome measure

The primary outcome measure will be the absolute change in aortic root diameter per year measured by echocardiography. Echo measurements will be taken by transthoracic echocardiograms (TTEs) performed at baseline and annually thereafter in order to assess the annual change of aortic dilatation.

#### Secondary outcome measures

The secondary outcome measures are as follows:

1. Change in Z-score per year, where the Z-score is calculated on aortic root and body surface area (BSA)

2. Clinical events and requirement for surgery including aortic dissection confirmed by transesophageal echocardiography (TEE), MRI, or CT, aortic dissection requiring emergency surgery, aortic dissection requiring elective surgery, aortic dilatation requiring elective or emergency surgery, death (all causes and classified by suspected cause), cerebrovascular accident, cardiovascular death, aortic regurgitation requiring surgery, or death during surgery for any of the above

3. Left ventricular function determined by volumes and ejection fraction

4. Left ventricular mass measurements

5. Assessment of valvular function

6. Cardiac rhythm and voltage

7. Height, weight, arm span, and lower segment measurements

8. Fibrillin-1 mutation analysis will be performed for those patients whose mutation status is unknown.

### Echocardiography

Aortic dilatation will be measured by echocardiography. All annual echocardiograms will be analyzed by an established echo core laboratory. Patients will be seen in centers that have routine access to standard M-mode, two-dimensional (2-D) echocardiography. Transthoracic M-mode, 2-D, and Doppler echocardiograms will be performed by experienced technicians, according to a standardized protocol. Each center will be trained on the standardized protocol prior to commencing the trial. Aortic root diameter will be measured at the annulus, in the sinuses of Valsalva at the tip of the open cusps at 90° to the direction of flow, the sinotubular junction, ascending aorta, aortic arch, and descending aorta.

Each echocardiogram will be sent electronically to the echocardiographic core laboratory at the John Radcliffe Hospital, Oxford, UK, where a single experienced investigator will supervise the reading and interpretation of all echocardiograms according to a standardized protocol to reduce variability due to observer variation. The echo core laboratory will be blinded to the study drug allocation to eliminate any bias in echo measurement. Quality control processes will be developed as part of the echo protocol. The echocardiographic protocol is included in Additional file 1.

### Fibrillin-1 mutation analysis at baseline

There is a 92% chance of finding a mutation in classical MFS. For patients who have not already had fibrillin-1 mutation screening, but who are considered clinically affected with MFS, a 5 mL EDTA blood sample will be collected and stored for assay. Samples will be analyzed and funded as per usual local arrangements.

Samples from units which do not have funding for these tests should be sent directly to the Sonalee Laboratory, St. George’s, University of London, London, UK [3]. Samples will be entered in the research program assay, and research laboratory reports will be issued.

A separate genetic sub-study will be undertaken to investigate the correlation between the response to medication and the site and type of mutation which determine the phenotype [4,39,40]. Patients will consent to this sub-study separately from the main trial.

### Additional investigations and sub-studies

To increase knowledge about the underlying disease and the potential mechanism of action of ARBs, several sub-studies are proposed. The main proposed sub-studies are:

1. Genetic sub-studies: a) fibrillin-1 mutation analysis; and b) pharmacogenetics sub-study

2. Total circulating TGF-β1.

### Data collection

#### Electronic case record form (eCRF)

Trial data will be captured on a web-based eCRF. The eCRF will be designed in accordance with the requirements of the trial protocol and will comply with regulatory requirements. Access to the eCRF will be password-protected.

#### Pharmacovigilance

The Royal Brompton and Harefield NHS Foundation Trust (Sponsor) has delegated responsibility for pharmacovigilance to the trial coordinating center, the CTEU of the Royal Brompton and Harefield NHS Foundation Trust. The CTEU will be responsible for recording all reported SAEs from investigational trial sites, and expedited reporting of SUSARs in accordance with statutory regulations.

#### Adverse event (AE)

An adverse event (AE) is defined as any untoward medical occurrence in a patient or clinical trial subject administered a medicinal product and which does not necessarily have a causal relationship with this treatment. An AE can therefore be any unfavorable and unintended sign (including an abnormal laboratory finding), symptom, or disease temporally associated with the use of an IMP, whether or not considered related to the IMP.

#### Adverse reaction (AR)

Adverse reactions (ARs) are all untoward and unintended responses to an IMP related to any dose administered. All AEs judged by either the reporting investigator or the sponsor as having reasonable causal relationship to a medicinal product qualify as ARs.

In the event an AR is reported during the trial, investigators will assess the severity of the AE using the following criteria, detailed on the AE report form in the eCRF:

1. Mild: awareness of signs or symptoms, but easily tolerated; are of minor irritant type; causing no loss of time from normal activities; symptoms would not require medication

2. Moderate: discomfort severe enough to cause interference with usual activities

3. Severe: inability to do work or usual activities; signs and symptoms may be of systemic nature or require medical evaluation and/or treatment.

### Unexpected adverse reaction (UAR)

An unexpected adverse reaction (UAR) is an AR, the nature or severity of which is not consistent with the applicable product information (summary of product characteristics, SmPC). When the outcome of the AR is not consistent with the applicable product information this AR should be considered as unexpected. Side effects documented in the SmPC which occur in a more severe form than anticipated are also considered to be unexpected.

### Expected drug-related AR

Expected drug-related ARs will be referred to the SmPC as provided and the summary in Additional file. Symptomatic hypotension defined as systolic blood pressure <90 mmHg in combination with dizziness and/or syncope on standing is considered an expected AR and will be reported on a specific AE form. Any other AR will be reported on a generic AE form on the eCRF.

### Reporting ARs

Investigators will report all ARs on the AE report form in the eCRF including information of the event, details of date of onset, frequency, severity, and potential relationship to treatment, outcomes, and action taken. Investigators will make a clinical judgement as to the appropriate action required depending on the severity of the reaction. This could include monitoring the patient over a period of time, interrupting the drug regime, discontinuing the patient from the trial, or continuing with the trial as specified. Investigators will submit AE reports to the CTEU after each patient visit. The CTEU will maintain a database of all ARs. AEs will be reviewed at regular intervals by the Data Monitoring Committee (DMC) for signal and trend analysis.

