### Statistical analysis

The primary analysis in this study is the comparison of the rate of annual aortic dilatation in those patients treated with irbesartan compared to placebo. The annual rate of dilatation will be calculated by estimates of mean values of the annual echocardiograms adjusting the time of follow-up to a 'common’ start point, that is, the baseline measurement. An independent samples *t*-test will be used to test for a difference in the rate between the irbesartan and placebo groups, assuming that the measurement of annual dilation follows a normal distribution. Analysis of covariance (ANCOVA) will be used if the analysis of the primary outcome is adjusted for any other variables. The primary analysis will be carried out according to the intention-to-treat principle in which all randomized patients will be included according to their initial randomized allocation irrespective of whether they continue to take the assigned treatment or not. Patients who are not followed up to the end of the study for whatever reason will have the last echo measurement included in the analysis. Patients will be followed from the time of randomization to the end of the study period. Thus individual patients will have a variable follow-up period. No formal method for imputing missing aortic diameter values is proposed as the comparison will be performed on the mean of group data. Secondary analyses include comparison of other measurements using appropriate comparative and descriptive statistics.

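### Investigators may take a patient out of the trial, not only off study drug, after an adverse reaction; echoes then stop, in tension with the intention-to-treat analysis

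*Protocol article*

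**What the plan says.** Four parts of the protocol article bear on this.

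- **Reporting ARs.** The investigator judges what to do according to the severity of the reaction. The options include "interrupting the drug regime, discontinuing the patient from the trial, or continuing with the trial as specified".
- **Temporary and Permanent discontinuation of IMP.** These concern the drug only. For example, "Patients may permanently withdraw from treatment with the investigational medicinal product (IMP) if they decide to do so". Neither section says whether the annual echocardiograms go on afterwards.
- **Withdrawal from trial procedures and incomplete follow-up.** "Investigators must ascertain the reasons for the withdrawal including discontinuation of study drug", and the list goes on to "withdrawal due to adverse events, failure to attend, non-compliance, withdrawal of consent, or other reasons". The section accepts that "Withdrawal from trial procedures may result in incomplete patient follow-up and failure to capture outcome data" and adds: "In these cases as much data as possible will be collected, up until the point of withdrawal".
- **Statistical analysis.** The primary analysis is by intention to treat and includes all randomized patients "irrespective of whether they continue to take the assigned treatment or not", with follow-up from randomization to the end of the study period. For incomplete follow-up, "Patients who are not followed up to the end of the study for whatever reason will have the last echo measurement included". No formal imputation is proposed.

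**The concern.** An intention-to-treat comparison of dilatation rates needs echoes taken after patients stop the drug. The Reporting ARs text gives the investigator a route by which a drug reaction ends the patient's participation, and the withdrawal text then ends data collection. Patients who react to the drug are those for whom off-drug measurements matter most.

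The protocol names symptomatic hypotension as an expected reaction (Expected drug-related AR), and gives hypotension and renal impairment as grounds for stopping the drug (Trial intervention; Temporary discontinuation of IMP). If such reactions are commoner on irbesartan, echoes would be lost more often in that arm, and for a reason linked to treatment. For those patients the analysis would estimate an on-treatment rate while being labelled intention to treat. Echoes that were never taken cannot be recovered by any analysis plan.

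**Working it through.** **1. Timing of removal against the echo schedule (Table 1).** The baseline echo is at visit 0 (month 1). Randomization to 150 mg or placebo is at month 2, and uptitration to 300 mg or placebo, where applicable, is at month 3. The first follow-up echo is at month 12.

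- *Removed between months 2 and 12:* only the baseline echo exists. A rate needs two measurements, so none can be calculated. With no imputation, the patient cannot enter the primary analysis. Here the aim of including all randomized patients fails outright, unless an unscheduled echo is obtained.
- *Removed after month 12:* the patient stays in the randomized arm through the last echo. The rate covers only the time before removal. If drug stop and removal coincide, it is an on-drug rate, from fewer echoes over a shorter time.

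**2. The planning figures.** From Sample size calculation: placebo rate 1 mm/yr, target difference 0.5 mm/yr, SD 1.8 mm, 5% significance (taken as two-sided), 80% power.

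n per arm = 2 × (1.96 + 0.8416)² × 1.8² / 0.5² = 2 × 7.849 × 3.24 / 0.25 = 203.4, rounded up to 204.

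This reproduces the protocol's 204, so 0.5 mm/yr is used below as the on-drug effect.

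**3. Illustration of size.** The following are assumptions, not figures from the documents: a share q of the irbesartan arm stops halfway through follow-up, reverts fully to 1 mm/yr, and is removed at that moment; there is no corresponding loss on placebo.

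- Rate of a stopper over full follow-up: 0.5 × 0.5 + 0.5 × 1.0 = 0.75 mm/yr.
- Mean of the irbesartan arm: (1 − q) × 0.5 + q × 0.75 = 0.5 + 0.25q.
- Intention-to-treat difference: 1 − (0.5 + 0.25q) = 0.5(1 − q/2).

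| q | Intention-to-treat difference (mm/yr) | Estimate if echoes stop with drug (mm/yr) | Overstatement |
|---|---|---|---|
| 10% | 0.475 | about 0.5 | 0.5/0.475 − 1 = 5% |
| 20% | 0.45 | about 0.5 | 0.5/0.45 − 1 = 11% |

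**4. Against the precision of the trial.** With 245 per arm, the standard error of the difference is 1.8 × √(2/245) = 0.163 mm/yr. The overstatement of 0.025 to 0.05 mm/yr is 0.025/0.163 = 0.15 to 0.05/0.163 = 0.31 standard errors.

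**The case against.** Three stronger readings are tempting, and the documents do not support them.

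- *That patients may be removed for non-compliance.* Reporting ARs does not mention it. The withdrawal section lists non-compliance, adverse events and drug discontinuation as reasons the investigator must record, not as rules for removal. The sample size section does count non-compliance within the 20% drop-out allowance, but that is not a removal rule either.
- *That the withdrawal text and the intention-to-treat text flatly contradict each other.* The Statistical analysis section provides for early leavers: they stay in their arm with their last echo. The conflict is strict only for patients with no follow-up echo. For the rest it is a tension, which the last-echo rule covers over without resolving.
- *That removal is known to differ by arm.* No removal rate is given for either arm. The four-week open-label run-in also screens out some intolerance before randomization. It uses 75 mg, however, so tolerance of the 150 mg and 300 mg doses is first tested after randomization.

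The rest of the case against has some weight. The drug-stopping sections are separate from the section on withdrawal from trial procedures, and a patient who does not tolerate 300 mg is downtitrated and stays in the trial. The Reporting ARs list is permissive and sits in a reporting paragraph. The withdrawal text promises as much data as possible, and long-term NHS follow-up is planned, though no echoes are described for it. A condensed article may also leave detail on follow-up after drug stop to the full protocol. That would excuse silence in the IMP sections. It does not excuse the Reporting ARs sentence, which states trial exit as an option in its own right.

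The illustration is only that. Setting q = 20% assigns to this one route a share of the irbesartan arm equal to the protocol's whole drop-out allowance, and the bias is well under one standard error.

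**Conclusion.** The point holds as a defect in the follow-up wording. As written, an adverse reaction can lead to exit from the trial, data then stop, and nothing says that echoes continue after the drug is stopped. This works against an analysis meant to include all randomized patients regardless of adherence. Removal before month 12 takes the patient out of the primary analysis; later removal leaves a pre-removal rate.

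Whether the loss would differ by arm is a plausible risk, not an established fact, and its size cannot be computed from the documents. The 5-11% overstatement rests on the assumed 10-20% stopping halfway, full reversion to the placebo rate, removal of every stopper, and no matching loss on placebo. It is worth correcting because the remedy is cheap and the lost echoes could not be recovered later.

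**What to change.** 1. In Reporting ARs, replace the option of taking the patient out of the trial with: *discontinuing study drug, with annual echocardiograms and event follow-up continuing*.
2. In the two IMP discontinuation sections and the section on withdrawal from trial procedures, state that stopping study drug, an adverse event or non-compliance does not by itself end follow-up. Follow-up ends only when the patient withdraws consent to it, or on death.
3. Keep the list of withdrawal reasons as a recording requirement. Deleting items would lose information needed to judge the missing data and would keep nobody in follow-up.

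No rule on when study drug is stopped changes, and patients keep the right to refuse further data collection. The cost is a wording amendment, a reminder to sites, and continued follow-up effort for patients off drug, at annual visits that the protocol already describes as routine care. Recruitment was still open according to Trial status, so the change could still protect later echoes.

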**Discussion:**

This is the first clinical trial to evaluate the ARB irbesartan versus placebo in reducing the rate of aortic root dilatation in MFS. Not only will this provide useful information on the safety and efficacy of ARBs in MFS, it will also provide a rationale basis for potentially lifesaving therapy for MFS patients.

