### Expected SAEs (as a result of the underlying disease)

Expected SAEs as a result of the underlying disease include: admission or procedure for MFS including treatment for cardiovascular, musculoskeletal, ocular, and thoracic complications; aortic dissection; aortic regurgitation requiring surgery; emergency or elective aortic root and/or valve replacement surgery; cerebrovascular accident; and cardiovascular death, sudden death, or death during surgery.

Expected SAEs will be reported as per the usual data capture requirements for the study and are not subject to expedited reporting.

Other SAEs which are not expected irrespective of causality will be subject to SAE reporting requirements. In the event of an SAE, investigators will report details on the SAE form on the eCRF including date of event, admissions, diagnosis details, date of discharge, or death. SAE reports must be completed within 24 hours of the investigator’s knowledge of the SAE. Investigators will be able to submit follow-up SAE reports should further information become available. Investigators will be expected to assess and assign causality and expectedness of each event on the form using the definitions described below. The CTEU will review all SAE reports. The Chief Investigator/deputy will review the SAE reports and inform the CTEU of the assessment.

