### Data Monitoring Committee (DMC)

All members of the DMC are independent of the trial. The DMC will meet prior to the start of the trial and then one and two thirds of the way through the trial, or as required thereafter. The DMC will be expected to develop, in agreement with the investigators, a charter outlining their responsibilities and operational details.

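### Sites report and the coordinating centre stores only adverse reactions, yet the DMC is to review adverse events, so some non-serious events judged unrelated have no stated recording route

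*Protocol article*

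**What the plan says.** All references are to the protocol article.

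- **Adverse event (AE)** uses the wide definition. It covers any untoward occurrence "temporally associated with the use of an IMP, whether or not considered related to the IMP".
- **Adverse reaction (AR)** narrows this by a causality opinion: "All AEs judged by either the reporting investigator or the sponsor as having reasonable causal relationship to a medicinal product qualify as ARs".
- **Reporting ARs** sets the collection rule: "Investigators will report all ARs on the AE report form in the eCRF". The form also takes onset, frequency, severity, potential relationship to treatment, outcome and action taken. The section adds "Investigators will submit AE reports to the CTEU after each patient visit".
- The same section then describes storage and review: "The CTEU will maintain a database of all ARs. AEs will be reviewed at regular intervals by the Data Monitoring Committee (DMC", with signal and trend analysis as the purpose.
- **Expected SAEs (as a result of the underlying disease)** treats serious events differently: "Other SAEs which are not expected irrespective of causality will be subject to SAE reporting requirements". Expected serious events go through the trial's usual data capture.
- The **Discussion** part of the abstract sets the aim: "Not only will this provide useful information on the safety and efficacy of ARBs in MFS".

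**The concern.** Within one section the unit of safety data changes from ARs, for reporting and storage, to AEs, for DMC review. A committee cannot look for trends in events that sites were never told to record.

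A placebo arm makes it possible to compare event rates between arms without anyone deciding what caused an individual event. A rule that records a non-serious event only if a blinded investigator thinks it related puts that opinion ahead of the randomized comparison. This matters here because the article itself says that safety evidence for this drug class in Marfan syndrome is not clear, describes the trial as a licensed product in new conditions of use, and enrols patients from age 6.

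**Working it through.** The article states no safety rate, power or sample size, so there is no figure to reproduce. The check sets the sections side by side.

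**1. The chain as written**

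| Step | Who | Unit named | Section |
|---|---|---|---|
| Report on the AE form | Investigators | ARs | Reporting ARs |
| Hold in a database | Coordinating centre (CTEU) | ARs | Reporting ARs |
| Review for signals and trends | DMC | AEs | Reporting ARs |

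By the article's own definitions, ARs are a subset of AEs. The third row needs data that the first two do not provide.

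**2. Is there a wider stream elsewhere?** The sentence about AE reports going to the CTEU after each visit might suggest one. However, the section on expected drug-related ARs places symptomatic hypotension on a specific AE form and any *other AR* on the generic AE form. The AR section ties severity grading on the AE form to an AR having been reported. The AE form is thus described only as the vehicle for ARs. No section tells sites to report a non-serious event judged unrelated.

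**3. What is captured without a causality filter**

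| Information | Section | Causality opinion needed? |
|---|---|---|
| Serious adverse events | Pharmacovigilance; Expected SAEs | No |
| Death, dissection, surgery, cerebrovascular accident | Secondary outcome measures | No |
| Systolic pressure below 90 mmHg with dizziness and/or syncope on standing | Expected drug-related AR | No, an AR by definition |
| Blood pressure, renal function, electrolytes, liver function, blood count | Table 1 (visits 1 and 2, titration visit, annual visits) | No |
| Other non-serious events judged related | Reporting ARs | Yes, recorded |
| Other non-serious events judged unrelated | None found | No stated route |

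Only the last row is the gap.

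**4. An example of what falls into it.** The article lists dizziness and lethargy as beta blocker side effects (Medical treatment) and lets patients continue beta blockers (Concomitant treatments and procedures). Its causality scale, introduced for serious events, names other concomitant treatment as a reason to grade an event unlikely to be related. Suppose a patient on both a beta blocker and study drug has dizziness without a systolic pressure below 90 mmHg. The event could be put down to the beta blocker and, under the rule as written, not recorded. It could equally be graded possible and recorded. The outcome rests on individual opinion.

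**5. The sponsor's role.** The AR definition lets either the investigator or the sponsor find an event related. The sponsor can do this only for events that reach it. A non-serious event that the investigator thinks unrelated, and so does not report, never gets that second assessment.

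**The case against.** The strongest reply is that this is loose drafting in a condensed article. The section speaks of AE reports, the form has a field for relationship to treatment (which would add less if every entry were already judged related), and the DMC is said to review AEs. Full collection may be what was intended and what the eCRF instructions require. This stands as a caution: the text does not prove that events go uncollected. It does not remove the contradiction, because the explicit instruction and the description of the database both say ARs. An analysis plan or a DMC charter cannot recover events that were never recorded.

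The second reply is that the most important safety data are captured anyway. That also stands, and it limits the point. A reader might infer that sites record only drug-related events of any kind. The articles on serious events, hypotension and scheduled tests rule that out.

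A reader might also infer that harm would be seen late because the DMC meets "then one and two thirds of the way through the trial, or as required thereafter". The documents do not support this. Two evenly spaced meetings do not contradict review at regular intervals, further meetings are allowed for, operational detail is left to a charter, and unexpected serious events must be reported within 24 hours.

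**Conclusion.** The point holds as an internal contradiction about non-serious safety data. The reporting and storage rule covers ARs, the review task covers AEs, and non-serious events judged unrelated have no stated recording route unless another form or scheduled test captures them. The by-arm comparison of those events could be incomplete and would depend on blinded attribution. This rests on reading the article's definitions as written and on no wider instruction standing in the full protocol or eCRF, which are not shown.

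No numerical size is claimed. A reader might infer a loss of power to see an excess of harm, but the documents give no event rates or attribution shares, and even the direction depends on what is assumed. Take true rates of 10% and 20% with 245 per arm, all but the 245 being assumptions:

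- All events recorded: 0.10/√((0.09 + 0.16)/245) = 3.13, and Φ(3.13 − 1.96) ≈ 88%.
- 40% of events called related in both arms, so 4% v 8% recorded: 0.04/√((0.0384 + 0.0736)/245) = 1.87, and Φ(1.87 − 1.96) ≈ 46%.
- 20% of background and 70% of excess events called related, so 2% v 9% recorded: 0.07/√((0.0196 + 0.0819)/245) = 3.44, and Φ(3.44 − 1.96) ≈ 93%.

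The filter could therefore weaken or sharpen a signal. What can be said is that the comparison would no longer be free of causality opinion.

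**What to change.** In the section on reporting ARs:

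1. State that non-serious AEs are recorded on the existing eCRF AE form irrespective of causality, with relationship to treatment kept as a separate field.
2. State that the CTEU database and the DMC's by-arm tables cover AEs and not only ARs. ARs can still be listed as a subset.

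If sites already record all AEs, only the wording changes. If they do not, recruitment was under way when the article appeared, so the date of the change should be documented and earlier non-serious data described as AR-only.

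The cost is somewhat more eCRF entry at existing visits and telephone contacts. No new visits, tests or efficacy looks are needed, and the DMC meeting schedule need not change.
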